### Care pathway

The NCS report from the Neurophysiologist will determine the severity of CTS and include treatment recommendations. The clinical management of patients will be at the discretion of the consultant clinical neurophysiologist or referring clinician informed by local guidelines for commissioning and best practice guidelines. Patients who are eligible for the study will fall into three categories: i) no further treatment recommended or required (watch and wait), ii) recommended for conservative treatment by splinting and/or corticosteroid injection; iii) recommended for surgical decompression.

i) No further treatment – patients in this group are expected to have very mild symptoms and NCS confirming a mild compression. They either do not require any conservative treatment or have declined the offer of conservative treatment such as corticosteroid injection.

ii) Conservative treatment – patients in this group are expected to have mild to moderate CTS based on NCS results and will be offered steroid injection and splints.

iii) Surgical treatment – patients in this group are expected to have moderate to severe CTS based on NCS results and self-reported symptom severity. These patients are likely to meet the current thresholds for surgical referral which are: referral to secondary care if symptoms are not resolved to patient’s satisfaction after 6 months of conservative treatment from date of 1st consultation with physician or if neurological deficit is present, i.e. sensory blunting or weakness of thenar abduction (APB).

During the 2 year follow-up, patients may undergo different treatments depending on the course of the CTS. For example a patient may be recommended not to have treatment when first enrolled however 6 months later symptom severity and associated disability may have increased necessitating conservative treatment. Or a patient may be treated with corticosteroid injection initially and progress to surgery in the course of the 2 years. Patients may also seek or be offered other treatments including alternative therapies.

All types of treatments received for CTS of either hand will be recorded by patients through 6 monthly self-report. To assist patients in the recall of treatments received a 6 months diary card will be issued in which they can record date, type, dosage and out of pocket expenditures for any treatments for CTS.

### Questionnaire data

Data on putative predictive factors will be collected with a study specific questionnaire through a combination of standardised measures and purposely designed questionnaires:

Symptom severity will be assessed with the 6-item short form of the Boston Carpal Tunnel Questionnaire, the CTS-6 [18].

Hand functional status will be assessed with three subscales of the Michigan Hand Questionnaire (MHQ) which capture unilateral and bilateral hand function, activities of daily living and work performance [19].

Psychological status has been identified as a predictor of outcome in several studies and will be measured using the standardised Hospital Anxiety and Depression scale (HADs) [20].

Health-related quality of life and health utility will be assessed by the EQ-5D-3 L (http://www.EuroQol.org). Results of the EQ-5D-3 L will be converted into utilities by applying UK specific preference weights to the health profiles. QALYs accrued will be calculated by integrating utility with respect to time. QALYs accrued in year two will be discounted by 3.5%.

Comorbidity will be assessed using a self-administered standardised Comorbidity Questionnaire developed by Sangha et al. [21].

Additionally, at baseline other clinical and sociodemographic factors will be collected through self-report including age, sex, ethnicity, work status and type of work, smoking status, alcohol use, household income.

Results from NCS will be requested from the neurophysiologist once patients have consented and been enrolled into the study. Median nerve sensory nerve action potential (amplitude and velocity) for digit III and distal motor latency (amplitude and velocity) will be recorded. Padua’s criteria [17,22] for classifying CTS severity according to the neurophysiology results will be used to grade severity from 1 to 6 (mild to extremely severe).

### Resource use and cost

Patients will be asked to complete a set of resource use questions asking about prescribed medications, primary, secondary and tertiary NHS and private healthcare contacts, alternative therapies and over the counter medicines purchased and time off work due to CTS since the last follow-up. The questionnaire completed at baseline will pertain to resource use in the three months prior to commencement of the study. Following completion of the baseline questionnaire and each follow-up (except final follow-up), patients will be issued with a 'resource use diary’ in the form of a card with tick-boxes and space for notes for patients to complete over the interim time period [23]. This will be used as an aide memoire when completing the resource use sections of the questionnaires.

To verify the patient-self-reported data, at the 2 year follow-up the General Practitioner of a random sample of at least 10% of patients will be contacted to confirm numbers of primary care contacts for CTS, whether the patient is still receiving treatment for CTS, details of drug and dosage where corticosteroid injection has been given, and other drugs prescribed for CTS. Records of surgery performed will also be extracted and compared with patient reported data.

### Outcomes

The primary outcome used to classify treatment successes and failures will be patient-reported global assessment of outcome (GAO) at 2 years using a 5 point ordinal scale: worse = 1, unchanged = 2, slightly better = 3, much better = 4, completely cured = 5. A grade of 3 or above will be defined as treatment success. Secondary outcomes include patient-reported clinical symptoms (CTS-6), functioning (MHQ), psychological health HADs, quality of life (EQ-5D) and resource use.

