Surgical decompression is effective in most patients, however reported success rates vary. An analysis of pooled results from 209 studies, representing 32,936 operations, found that 75% of patients considered themselves improved, much better or cured [13]. Misdiagnosis and surgical errors such as incomplete decompression are the most common reasons for failure. The answer to the question of what factors predict a good surgical outcome has so far eluded us.

The authors of a recent systematic review of surgical and non-surgical treatments concluded that future research needed to focus on 'prognostic studies which lead to better patient characterisation and the identification of predictive factors that indicate likely response to specific treatments’ [14]. Although a number of studies have explored prognostic factors, these have been conducted either retrospectively or in the context of randomised trials which has limitations [15]. To date no prospective cohort study of prognostic factors has been undertaken. The value of high quality prognostic research is that it leads to a better understanding of disease progression, better targeting of effective treatments that mitigate progression and allows more reliable information about the risk of a negative outcome to be communicated to patients [15]. A cohort study of prognostic factors would be the first necessary step towards the development and further external validation of clinical prediction rules. This work would also address the need to focus on outcomes that matter to patients as outlined in the NHS Outcomes Framework [16] by collecting patient-reported outcomes on one of the commonest elective surgical procedures in the upper extremity.

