### Sample size

An estimated 1200 patients are seen at the Norfolk and Norwich University Hospital (NNUH) each year with suspected carpal tunnel syndrome. Of these, at least 85% (around 1020) will be confirmed as having CTS through NCS indicating a mild or worse compression. Assuming a recruitment rate of 75%, which is not unreasonable, given previous experiences, we would expect to recruit around 765 CTS subjects per annum, i.e. 1530 over the two year recruitment period. It is estimated that around 30% (460) will go to surgery immediately and 70% (1070) will be treated with corticosteroid injection. Of the latter, it is expected that, by two years follow-up, two thirds will have been referred for surgery, whereas the remaining third (about 355) will be considered a success. There is no standard agreed method for calculating sample sizes or statistical power for logistic regression models. However, following the approach by Demidenko [24] a sample size of 1070 would confer 90% statistical power, assuming a 33% success rate, to detect an increase in success with an odds ratio of 1.51 for an explanatory binary variable with an even split in classification (i.e. an equal number of subjects in each group). For an uneven split, this odds ratio would be smaller. Should recruitment be less than expected, a sample size of 535 (i.e. half that expected) would confer 90% power to detect an odds ratio of 1.79.

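### The primary outcome and the sample size define success differently for injection-treated patients, so the stated power belongs to an endpoint that the plan does not analyse

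*Protocol article*

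**What the plan says.** The Protocol article (Outcomes) makes the primary outcome the "patient-reported global assessment of outcome (GAO) at 2 years using a 5 point ordinal scale" and adds: "A grade of 3 or above will be defined as treatment success". Grade 3 is the slightly-better category. No rule is given for treatment received between enrolment and the rating. The Analysis section models this outcome by binary logistic regression, also without such a rule.

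The Care pathway section expects treatment to change during follow-up: "Or a patient may be treated with corticosteroid injection initially and progress to surgery in the course of the 2 years".

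The Sample size section estimates that "around 30% (460) will go to surgery immediately and 70% (1070) will be treated with corticosteroid injection". Of the injected patients it expects that "by two years follow-up, two thirds will have been referred for surgery, whereas the remaining third (about 355) will be considered a success". That third supplies the planning rate: "a sample size of 1070 would confer 90% statistical power, assuming a 33% success rate", for an OR of 1.51 on an evenly split binary predictor. With 535 patients the detectable OR is given as 1.79.

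**The concern.** The two sections classify the same patient in opposite ways. An injected patient who is later operated on and feels much better at 2 years is a treatment success under Outcomes and not a success under Sample size. On the plan's own figures the group concerned is large: two thirds of 1070, about 713 patients, are expected to be referred.

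Two things are at stake.

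- **Interpretation.** Aims and objectives asks for predictors of response to injection and to surgery. Background and Discussion ask who gets lasting relief from injection and who will ultimately need an operation. The 2-year GAO on its own cannot separate a lasting response to injection from improvement after later surgery.
- **Planning.** The 33% rate, and the power built on it, belong to freedom from surgical referral. The Analysis section does not model that endpoint.

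**Working it through.** **Inputs.** From Sample size: n=1070 injected (fallback 535), 33% success, OR 1.51 (fallback 1.79), even split, 90% power, two thirds referred for surgery. From Background: 75% improved after surgery, in pooled surgical studies ("found that 75% of patients considered themselves improved, much better or cured"). Assumed, because not stated: two-sided 5% test, and 33% as the rate in the reference group.

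**Step 1: reproduce the plan's figure.** Wald test of the log odds ratio, n/2 per group:

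- p1 = 0.33; odds 0.33/0.67 × 1.51 = 0.7437; p2 = 0.7437/1.7437 = 0.4265.
- SE = √[1/(535 × 0.33 × 0.67) + 1/(535 × 0.4265 × 0.5735)] = 0.1269.
- Power = Φ(ln 1.51/0.1269 − 1.96) = Φ(1.288) = 90.1%.
- For n=535 and OR 1.79: p2 = 0.4685, SE = 0.1787, power 90.3%.

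Both stated figures are right for the no-referral endpoint. Reading 33% as the overall rate gives 88.2% and 87.7%.

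**Step 2: success rate on the GAO.** Let s be the share of referred patients who rate 3 or above. Assume that all non-referred patients do so and that all referred patients are operated on.

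- GAO rate = 0.33 + 0.67 × s. With s = 0.75 it is 0.8325.
- In counts: 713 × 0.75 ≈ 535 successes after surgery, plus 357 without, gives 892/1070 = 83%. Of these, 535/892 = 60% would have had surgery. (That this 535 equals the fallback sample size is a coincidence.)

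**Step 3: OR detectable with 90% power at n=1070, by s.**

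| s | GAO success | Rate read as overall | Rate read as reference group |
|---|---|---|---|
| 0.25 | 50% | 1.49 | 1.49 |
| 0.50 | 67% | 1.53 | 1.56 |
| 0.75 | 83% | 1.72 | 1.82 |
| 0.90 | 93% | 2.35 | 2.94 |

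At 83% success, power for OR 1.51 is about 70% (overall) or 64% (reference group). At n=535 the detectable OR is about 2.2 to 2.5 instead of 1.79.

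**Step 4: what happens to a predictor of injection response.** Take a factor with OR 1.51 for success without surgery (0.33 v 0.4265) and s = 0.75 in the reference group.

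- If it has no effect on surgical outcome, the GAO rates are 0.8325 and 0.4265 + 0.5735 × 0.75 = 0.8566. The OR is (0.8566/0.1434)/(0.8325/0.1675) = 1.20. With SE 0.169, power is 19%. Changing s alone gives 40% (s = 0.50), 27% (0.65) and 13% (0.85).
- If it also predicts surgical success, s in the other group rises:

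| OR for surgical success | s, other group | GAO rate, other group | GAO OR | Power |
|---|---|---|---|---|
| 1.2 | 0.783 | 0.875 | 1.41 | 51% |
| 1.3 | 0.796 | 0.883 | 1.52 | 65% |
| 1.51 | 0.819 | 0.896 | 1.74 | 86% |

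**The case against.** **The Outcomes section is silent; it does not say that intervening treatment is ignored.** This is true, and how crossovers are allocated between an injection model and a surgery model is a detail that an article may leave to the full protocol or analysis plan. But both definitions of success are stated in this article and they disagree, so any fuller document must depart from one of them.

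**The power calculation is sound.** For its own endpoint it is; the fault is the mismatch.

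**The 83% is soft.** This stands. Referral is not the same as operation, some non-referred patients will rate below 3, and the 75% comes from pooled surgical studies with different outcome wording. At 50% GAO success the detectable OR would be no worse than planned.

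**Stronger readings.** A reader might infer that the GAO endpoint necessarily biases predictor effects toward the null and that power drops to 19%. The documents do not support this. The 19% requires a factor with no effect on surgical outcome. Yet Background links longer duration and greater severity to poorer surgical results (calling the evidence equivocal), and Discussion cites symptom severity as a predictor after both treatments. In that case the GAO OR can exceed 1.51.

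A reader might also infer that the rating should be re-anchored to the date of surgery. A fixed 2-year outcome is consistent with the stated aims. The article states the GAO only at 2 years, and the last questionnaire is at 24 months. A rule needing six months after surgery would leave anyone operated on after month 18 without an outcome.

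**Conclusion.** The inconsistency stands and affects the primary endpoint. Outcomes and Analysis use the 2-year GAO with no condition on surgery; Sample size uses freedom from surgical referral. The stated 90% power therefore does not apply to the outcome to be modelled.

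How far the detectable OR moves cannot be fixed from the article. The rise from 1.51 to about 1.72 to 1.82 rests on the three Step 2 assumptions: all non-referred patients rate 3 or above, all referred patients are operated on, and 75% of those rate 3 or above. Dilution of predictor effects is possible but conditional: OR 1.20 with 19% power if the factor does not affect surgical outcome, and OR 1.41 to 1.74 with 51% to 86% power if it predicts surgical success with OR 1.2 to 1.51. What does not depend on any of these assumptions is that the two sections must be reconciled.

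**What to change.** Reconcile Outcomes and Sample size before any analysis, in one of two ways.

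1. **Preferred for the injection model.** Define success as GAO 3 or above at 24 months with no CTS surgery by then (or no referral for it, but the same term in every section). Report GAO 3 or above regardless of later treatment as a secondary outcome. Restate the planning success rate and detectable OR for this composite.
2. **If GAO regardless of later treatment stays primary.** Replace the 33% with a justified rate for that endpoint, with a range, and restate the power. Say plainly that the model predicts 2-year status and not response to injection alone.

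The cost is a wording change in Outcomes, Sample size and Analysis, plus a rerun of the power calculation. Treatments received are already recorded by six-monthly self-report, so surgery status needs no new collection; a referral-based rule would need a check that referral is captured. There are two downsides to the first option. The composite rate may fall below 33% if some unreferred patients score under 3. It also relies on self-reported surgery: the Resource use and cost section provides for comparison with surgery records, but does not make clear that this covers every patient and not just the random sample of at least 10%.

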## Abstract

**Background:**

Carpal tunnel syndrome (CTS) is the most common neuropathy of the upper limb and a significant contributor to hand functional impairment and disability. Effective treatment options include conservative and surgical interventions, however it is not possible at present to predict the outcome of treatment. The primary aim of this study is to identify which baseline clinical factors predict a good outcome from conservative treatment (by injection) or surgery in patients diagnosed with carpal tunnel syndrome. Secondary aims are to describe the clinical course and progression of CTS, and to describe and predict the UK cost of CTS to the individual, National Health Service (NHS) and society over a two year period.

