## Background

Carpal Tunnel Syndrome (CTS) is the commonest peripheral entrapment neuropathy which causes pain, tingling, numbness and weakness in the distribution of the median nerve of the hand. It is bilateral in 55-65% of cases [1] and is a significant contributor to impaired hand function and work disability. In the UK in 2000 the annual age standardised rate per 100,000 was 87.8 for men and 192.8 for women [2]. There are no estimates of the cost of CTS to UK society or the NHS, however societal costs to the USA of patients undergoing decompression surgery were estimated at over $2bn in 1995 [3]. More recently in 2007, the income loss per CTS patient over a period of 6 years was estimated at $45,000-89,000 compared with controls (upper extremity fracture and dermatitis) [4].

Treatment options which are supported by high quality evidence are corticosteroid injection for mild to moderate symptoms [5,6] and surgical decompression in moderate to severe cases [7]. Surgery rates in 1995 in the UK were 71 per 100,000 [8] and rising to 90/100,000 a decade later [9]. Although steroid injection is an effective and relatively safe first line of treatment, its benefit beyond 8 weeks has not been demonstrated [5]. A UK study by Latinovic found that 31% of patients proceeded to surgery within 1 year of initial presentation to their General Practitioner [2]. A study in the Netherlands found that only 25% of patients had a good outcome at 1 year after steroid injection [10]. Similarly, Meys et al. [11] reported that 67% of patients treated by injection required surgery by 1 year. Surgical rates vary from country to country and depend on referral criteria. The introduction of 'low priority procedure’ thresholds by NHS trusts in England may account for lower surgery rates in the UK compared to the US or Europe.

The treatment algorithm currently used by most NHS Trusts in England is to refer patients to surgery only when symptoms are severe and disabling or when steroid injections have failed. Where injection fails to resolve symptoms, this prolongs the duration of symptoms and associated disability as well as incurring direct and indirect costs. As yet it is not possible to predict which patients will obtain long-term relief from steroid injection and which will require surgical decompression. Longer duration of symptoms and greater severity of symptoms are also associated with poorer surgical outcomes although the evidence seems equivocal [12].

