## Discussion

CTS is the most common nerve entrapment disorder of the upper limb which can lead to considerable hand disability and sickness absence in those working, yet little is known about the cost of CTS to the individual, NHS or society. A range of effective treatment options are available including conservative and surgical interventions. However it is not known which patients are more likely to benefit from what treatment. This prognostic study will provide important information about what baseline factors may predict a good long-term response to conservative treatment and which patients may ultimately require surgery. It is an important first step in building a multivariable model, which can be externally validated in future studies. The value of high quality prognostic research is that it leads to a better understanding of disease progression, better targeting of effective treatments that mitigate progression and allows more reliable information about the risk of a negative outcome to be communicated to patients [15].

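### Counting 'slightly better' as treatment success is looser than the good outcome the study sets out to predict, and it is not the success event behind the 33% in the sample size

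*Protocol article*

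**What the plan says.** The primary outcome is a patient-reported global assessment at 2 years, scored "worse = 1, unchanged = 2, slightly better = 3, much better = 4, completely cured = 5" (Outcomes). It is then split: "A grade of 3 or above will be defined as treatment success". The Analysis section makes a binary logistic model of this outcome primary. A proportional-odds model on all five grades is to be considered as a secondary analysis.

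The abstract gives the aim as to "identify which baseline clinical factors predict a good outcome from conservative treatment (by injection) or surgery". The Discussion says the study will show "what baseline factors may predict a good long-term response to conservative treatment", and its closing paragraph again speaks of a good outcome from both kinds of treatment.

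The Sample size section expects that, of 1070 patients treated by injection, by two years "two thirds will have been referred for surgery, whereas the remaining third (about 355) will be considered a success". Power is then stated "assuming a 33% success rate, to detect an increase in success with an odds ratio of 1.51".

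**The concern.** Three descriptions of success stand in the article, and they differ.

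- **Aim:** a good outcome, or a good long-term response.
- **Primary outcome:** any improvement at 2 years, however small.
- **Sample size:** no referral for surgery within 2 years of injection.

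The first two differ in strictness. A patient who is only slightly better after two years does not plainly have a good outcome, and the article gives no reason for cutting at grade 3. The fitted model would estimate the chance of any improvement, while its results are meant to inform patients and care pathways about a good result.

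The second and third differ in kind. A patient who is injected, later operated on and then improves is a failure in the Sample size section and a success under Outcomes. The 33% therefore says nothing direct about how often grade 3 or above will occur, and the power statement does not describe the primary model as defined.

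**Working it through.** **Inputs from the Sample size section:** N = 1070, success rate 33%, odds ratio (OR) 1.51, binary predictor split evenly, power 90%; fallback N = 535 and OR 1.79. No significance level is given there, so I assume two-sided 5%.

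**Step 1. Reproduce the stated power.** I use the Wald test of the log odds ratio, with 33% as the rate in the reference group.

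- p0 = 0.33; p1 = 1.51 × 0.33 / (0.67 + 1.51 × 0.33) = 0.4265
- Variance = 1/[535 × 0.33 × 0.67] + 1/[535 × 0.4265 × 0.5735] = 0.00845 + 0.00764 = 0.0161; SE = 0.127
- z = ln(1.51)/0.127 = 0.412/0.127 = 3.25; power = Φ(3.25 − 1.96) = 90.1%

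The same steps for N = 535 and OR 1.79 give 90.3%. If 33% is read as the overall rate, the results are 88.2% and 87.7%. The arithmetic is sound; the question is which event has the 33%.

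**Step 2. Vary the success rate.** The article gives no distribution of the five grades, so each rate below is an assumption. N = 1070, the rate applies to the reference group, and the other settings are as above.

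| Success rate | Power for OR 1.51 | OR detectable with 90% power |
|---|---|---|
| 33% | 90.1% | 1.51 |
| 50% | 91.5% | 1.49 |
| 67% | 85.7% | 1.56 |
| 75% | 78.3% | 1.64 |
| 83% | 64.8% | 1.81 |

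The 83% row uses figures in the article. Suppose every patient not referred counts as improved, all referred patients are operated on, and these improve at the pooled 75% in the Background. Success is then 1/3 + 2/3 × 0.75 = 0.83. Read as an overall rate instead, 83% gives power of about 71% and a detectable OR of about 1.71.

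**Step 3. Does the loose cut weaken predictor effects?** Take a factor with OR 1.51 for grades 4–5 (33% against 42.65%) and suppose 10% to 25% of patients are 'slightly better'. The answer depends on how those patients are spread over the two predictor groups.

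- **Same share in both groups.** At 10%: 43% against 52.65%, OR 1.47. At 25%: 58% against 67.65%, OR 1.51. Power is 88–90%.
- **Exact proportional odds.** OR stays at 1.51; power is 90–92%.
- **Factor has no effect on reaching grade 3 among patients below grade 4.** At 10%: 43.8% against 51.9%, OR 1.38. At 25%: 59.9% against 65.7%, OR 1.28. Power falls to 75% and 50%.

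Only the third pattern produces material dilution, and nothing in the article supports it over the other two.

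**The case against.** The cut-point is partly a matter of judgement. Nowhere does the article define a good outcome as 'much better' or 'completely cured'. Its own surgical benchmark of 75% counts patients who were merely improved, and the Aims section speaks more broadly of outcome and of response to treatment. The ordinal model keeps the grades apart, and symptom, function and quality-of-life scores are modelled too. The study is presented as a first step towards a model for external validation. All this stands, and it keeps the point modest. It does not supply a reason for grade 3, and the ordinal model is only secondary, resting on an assumption the authors themselves call hard to verify.

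A reader might infer more than the article supports, in three ways.

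- **That the study was planned on success rates of 25–33%.** Only 33% enters the sample size. The statement that "only 25% of patients had a good outcome at 1 year after steroid injection" is cited background.
- **That the loose cut certainly dilutes associations and costs a large part of the power.** Steps 2 and 3 show this only under particular assumptions; at 50% success, power is no lower than stated.
- **That moving the cut to grade 4 would restore the 33%.** It would not. The 33% is a rate of non-referral, not a global assessment rate at any cut. A patient operated on who ends much better is still a failure in one section and a success in the other.

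**Conclusion.** The concern holds in a limited form. The primary binary outcome counts any improvement at 2 years as success, which is looser than the good outcome the study says it will predict. It is also a different event from the one that supplies the 33%. Neither statement needs a numerical assumption.

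The size of the consequence is uncertain. The stated 90% power is correct for a 33% rate but is not tied to grade 3 or above. Power for OR 1.51 at N = 1070 runs from about 92% to 65% as the success rate goes from 50% to 83%, and where the true rate lies cannot be told from the article. These figures rest on a two-sided 5% test, an evenly split predictor and the rate applying to the reference group. The change is worth making because it is cheap and brings the outcome into line with the aim, not because a loss of power has been shown.

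**What to change.** 1. Define primary success as grade 4 or 5, with grade 3 or above as a prespecified sensitivity analysis. If grade 3 or above is kept as primary, say why and prespecify the grade 4–5 model alongside the ordinal model.
2. Reconcile the Outcomes and Sample size sections on what counts as success. In particular, say how a patient who is injected, later operated on and improved is classified.
3. Restate the expected success rate, with its source, and the detectable odds ratio for the definition kept, and give the significance level. If no rate is available, give a range as in Step 2.

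The cost is a few lines of text and one repeat of the model on data already collected. With grades 4–5 as primary, the headline success rate will be lower and less comparable with studies that count any improvement; the sensitivity analysis covers that.
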